## Abstract

Supplemental Digital Content is available in the text

## Introduction

1

Chronic prostatitis/chronic pelvic pain syndrome (CP/CPPS) is a common disorder with 4 domain manifestations: urogenital pain, lower urinary tract symptoms, psychological issues, and sexual dysfunction.^[1]^ Men of all ages and races may experience prostatitis, with a worldwide prevalence of 2% to 10%,^[2]^ while the prevalence is 15% to 16% in Asia, Europe, and North America.^[3]^ More than 90% of patients with symptomatic prostatitis have CP/CPPS.^[4]^ The first-line treatments for CP/CPPS include antibiotics, α-adrenergic antagonists, and simple analgesics.^[5]^ However, due to the multifactorial nature of this syndrome, no single therapeutic option is adequate and multimodal therapies are needed.^[6,7]^

Currently, there are many management approaches for CP/CPPS.^[8]^ According to previous studies, acupuncture has shown promise for the amelioration of CP/CPPS symptoms, particularly for relieving pain.^[9–12]^ The National Institutes of Health (NIH) Chronic Prostatitis Symptom Index (CPSI)^[13]^ is a valid and easily self-administered outcome measure for men with chronic prostatitis. Our previous pilot study^[14]^ showed that after 8 weeks of treatment, acupuncture was associated with a clinically significant decrease in the NIH-CPSI total score. However, in recent studies the change from baseline of the NIH-CPSI after acupuncture treatment has ranged widely,^[15–21]^ and higher than the minimal clinically important difference of the NIH-CPSI is 4 points.^[22,23]^ The results of these studies have been highly variable.

The primary presentation of CP/CPPS is urological pain,^[4]^ and pain is a predominant topic of research in acupuncture.^[24]^ Studies have shown that acupuncture has an immediate pain-relieving effect.^[25]^ The range of results of previous studies for the efficacy of acupuncture treatment in CP/CPPS may be due to differences in timepoints, places of assessment, and especially the subjective scales used for assessment.

### Objective of this study

1.1

This study will determine the efficacy of acupuncture treatment for patients with CP/CPPS after 4 weeks of treatment, and evaluate 3 modes of assessment of efficacy.

## Methods

2

### Study design

2.1

This trial is designed as a randomized sham-controlled multicenter trial with 2 parallel groups. It will be conducted at the following 5 hospitals: Guang’anmen Hospital, West China Hospital of Sichuan University, Yantai Hospital of Traditional Chinese Medicine, Hengyang Hospital Affiliated to Hunan University of Chinese Medicine, and The First Hospital of Hunan University of Chinese Medicine. The development of the study protocol conformed to the guidelines of the Standard Protocol Items: Recommendations for Interventional Trials (SPIRIT)^[26]^ and the Standards for Reporting Interventions in Clinical Trials of Acupuncture (STRICTA).^[27]^ This study will be conducted in accordance with the principles of the Declaration of Helsinki^[28]^ and has been approved by the Ethics Committee of Guang’anmen Hospital (Ethical number 2018-098-KY, see Table 1, Supplemental Content, which illustrates the ethical documentation) and the Research Ethics Committee of the aforementioned hospitals.

This trial has been registered at www.clinicaltrials.gov (NCT 03641807).

### Randomization and blinding

2.2

All the subjects of this study will fulfill the inclusion criteria and provide written informed consent before enrollment. The enrollees will be randomly assigned, by computerized simple random sampling, to receive either acupuncture or sham acupuncture at a population ratio of 1:1. The allocation sequence will be generated by the Institute of Basic Research in Clinical Medicine affiliated to China Academy of Chinese Medical Sciences. The participants, outcome assessors, and statisticians will be blinded to the allocation. The flowchart is shown in Fig. 1 and the timepoints of enrolment, interventions, and assessments are shown in Fig. 2.

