### Study population and recruitment

2.3

Sixty participants will be recruited from September 2018 to September 2019 through posters, hospital websites, and networks. Recruitment will be conducted by research assistants.

Each participant will have a medical history, physical examination, prostatic fluid cultures, prostate-specific antigen evaluation, urine flow rate, and residual urine examination. Microbiology of the prostatic fluid/urine specimen will be collected by the 2-glass test.^[29]^ A urologist will be responsible for diagnosis.

The criteria for inclusion in this study are the following: aged 18 to 50 years; with CP/CPPS, diagnosed according to the NIH CP/CPPS consensus (discomfort or pain in the pelvic region ≥3 months during the previous 6 months^[4]^); and NIH-CPSI total score ≥15. Potential participants will be excluded for any of the following: urologic disease; residual urine volume ≥100 mL, Qmax ≤15 mL/s; use of 5-alpha reductase inhibitor, alpha-blockers, antibiotics or any other prostatitis-specific medication during the previous 1 month; diseases that influence urologic symptoms; or any acute disease or severe disease requiring treatment. Urologic diseases that will prevent inclusion are bladder outlet obstruction, overactive bladder, neuropathic bladder, interstitial cystitis, cystitis glandularis, bladder cancer, acute prostatitis or bacterial prostatitis, benign prostatic hyperplasia, prostate cancer, symptomatic urinary tract infection, and organic diseases of urinary system. Diseases that influence urologic symptoms are multiple sclerosis, multiple system atrophy, stroke, Alzheimer disease, Parkinson's disease, spinal cord injury, cauda equina injury, and sexually transmitted disease.

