### Calculation of sample size and statistical analyses

2.7

We hypothesize that acupuncture will be more effective than sham acupuncture, according to at least one assessment mode, at week 4 after treatment. Based on the results of a previous electroacupuncture study,^[14]^ we estimated that 28 patients were required in each group to provide 90% power to detect a difference of 4 in the NIH-CPSI total score, with a standard deviation of 4.5 at a 2-sided alpha level of 0.05. Accounting for a 6% loss during follow-up, we calculated that we would need to enroll 60 patients.

All efficacy analyses were performed on an intention-to-treat population, and included all patients who were randomly assigned, regardless of whether they received treatment. Safety analyses were defined as all patients who received at least one treatment session. We analyzed the change from baseline in the NIH-CPSI total score by fitting a general linear model, with the baseline value as a covariate, and treatment as a fixed effect. The same approach was used for the 3 key secondary outcomes and the change from baseline in the IPSS score. Categorical variables were compared using Fisher exact test or the Wilcoxon rank-sum test, as appropriate.

To account for multiplicity to test the 3 primary hypotheses and the 3 secondary hypotheses, a hierarchical procedure for multiple testing was used to control the overall type I error rate. For further details, see Table 2, Supplemental Content, which illustrates the Hierarchical procedure for multiple testing, in 6 steps.

Missing data on the primary outcome were assumed due to random occurrence and were imputed using the multiple imputation method. All statistical analyses were performed using Statistics Analysis System version 9.4 software (SAS Institute) with 2-sided tests at a significance level of 0.05.

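### Sixty patients at five hospitals are allocated by simple randomisation and analysed without a hospital term: a valid test that gives up some precision at little saving

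*Protocol article*

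**What the plan says.** Protocol article, 2.1 Study design, describes a "randomized sham-controlled multicenter trial with 2 parallel groups" and names the sites: "It will be conducted at the following 5 hospitals". Section 2.3 gives the total: "Sixty participants will be recruited from September 2018 to September 2019".

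Section 2.2 states that enrollees are "randomly assigned, by computerized simple random sampling, to receive either acupuncture or sham acupuncture at a population ratio of 1:1". It names no block and no stratum.

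Section 2.7 fits a general linear model to the change in NIH-CPSI total score, "with the baseline value as a covariate, and treatment as a fixed effect". It uses the same approach for the key secondary outcomes and the IPSS change. Hospital is not among the terms listed.

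The sample size in 2.7 is also explicit: "we estimated that 28 patients were required in each group to provide 90% power". The inputs given there are a 4-point difference, an SD of 4.5 and two-sided alpha 0.05, and an allowance of 6% for loss brings enrolment to 60.

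Both the allocation method and the model terms are stated outright, so neither is simply a detail left to a fuller document.

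**The concern.** Hospital is a plausible source of variation here. Treatment is manual needling with repeated manipulation until a sensation is reported (2.4.1), and the outcome is a symptom scale that two of the three assessment modes record at the hospital (2.5). The Discussion itself says that the assessors' presence and situational factors may affect the response. That acupuncturists and assessors differ from one hospital to the next is an inference; the article does not say so.

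Simple randomisation does nothing to balance arms within a hospital, and with few patients per site sizeable splits are to be expected. Without a hospital term, any difference between hospitals stays in the residual and widens the confidence interval. At stake is precision in a trial whose Discussion already lists small sample size as a limitation.

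**Working it through.** **Inputs.** From 2.1, 2.3 and 2.7: five hospitals, N = 60, difference 4, SD 4.5, two-sided alpha 0.05, 28 per group, 6% loss. Assumed, because the article does not give them: 12 patients per hospital (other sizes below) and the share of outcome variance due to hospital.

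**1. The plan's own figure.** Two-sample t test, noncentrality 4 / (4.5 × √(2/n)):
- n = 27: noncentrality 3.266, power 0.893
- n = 28: noncentrality 3.326, power 0.904

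So 28 per group reproduces. Enrolment: 56 / 0.94 = 59.6, rounded up to 60. This also reproduces.

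**2. Overall arm imbalance and its cost.** X ~ Binomial(60, 0.5), with power from the noncentral t at all 60 patients:

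| Split | P(this or worse) | Power |
|---|---|---|
| 30:30 | – | 0.923 |
| 33:27 | 0.519 | 0.920 |
| 36:24 | 0.155 | 0.913 |
| 38:22 | 0.052 | 0.904 |
| 39:21 | 0.027 | 0.898 |

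Average power under simple randomisation is 0.919. With 56 evaluable patients the average is 0.899, against 0.904 at 28:28.

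**3. Imbalance within hospitals.** X ~ Binomial(12, 0.5):
- 9:3 or worse at one given hospital: 2 × P(X ≤ 3) = 0.146; at one or more of five: 1 − (1 − 0.146)^5 = 0.55
- 8:4 or worse: 0.388 at one hospital; 0.91 at one or more of five

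Varying the assumed sizes (12 × 5; 20/10/10/10/10; 24/12/12/6/6; 36/6/6/6/6), the chance that at least one hospital splits 2:1 or worse is 0.84 to 0.99.

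**4. Stratified allocation with a hospital term, 28 per arm.** If 4.5 is the total SD and hospital explains a share s, the residual SD is 4.5 × √(1 − s), with 56 − 2 − 4 = 50 df:

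| s | Residual SD | Power |
|---|---|---|
| 0 | 4.50 | 0.903 |
| 5% | 4.39 | 0.917 |
| 10% | 4.27 | 0.930 |
| 15% | 4.15 | 0.943 |

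The comparator is 0.904 as planned. If 4.5 is instead the within-hospital SD, the total SD is 4.5 / √(1 − s), and the model without hospital has power 0.889 (s = 5%) or 0.873 (s = 10%).

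**5. Validity.** In simulations of simple randomisation without a hospital term (five hospitals of 12, s from 0 to 20%, 4,000 runs each), type I error was 0.047 to 0.053.

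**6. Hospital term added after simple allocation, N = 60.** At s = 0, average power is 0.898 with the term and 0.919 without. In simulation, the figures with and without the term were 0.913 and 0.922 at s = 5%, equal at 0.920 at s = 10%, and 0.950 and 0.920 at s = 20%.

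**The case against.** The strongest reply is that nothing here invalidates the trial. Type I error is held, chance imbalance is random error already reflected in the standard error, and the estimate is unbiased on average. That stands.

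A reader might infer that the sample-size requirement fails about half the time, since an arm falls below 28 with probability 0.52. The documents do not support this. With 60 enrolled, power before any loss drops below 0.90 only at 39:21 or worse, which has probability 2.7%. The wording in 2.2 could also mean drawing exactly 30 of 60, in which case overall imbalance disappears. Only the within-hospital point survives both readings: drawing 30 of 60, at least one of five hospitals of 12 still splits 8:4 or worse with probability 0.82.

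The gain is also uncertain. The article gives no between-hospital variance, and the gain is nil if hospitals do not differ. Whether 4.5 already contains hospital variance cannot be seen. The planned baseline adjustment may absorb some of it, and the standardised training in 2.4 and 2.8 is meant to limit operator variation. Mode 2 is recorded away from the hospital, so assessor differences bear less on it. These points limit the size of the benefit but do not remove it.

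Finally, the Discussion concedes that acupuncturists are hard to blind. Simple randomisation is the least predictable scheme, and blocks within small sites make late allocations easier to guess. That is a real trade-off, manageable with varying, concealed block sizes.

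**Conclusion.** The point holds as a modest precision issue. The stated allocation makes imbalance within hospitals very likely, and the stated model leaves any hospital variance in the error. The improvement on offer is about 1 to 4 power points if hospital explains 5% to 15% of variance, for about 0.1 point if it explains none. These figures assume that 4.5 is the total SD and that the hospital share lies in that range; the imbalance probabilities assume hospital sizes the article does not give.

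Two stronger conclusions should not be drawn: that the treatment estimate is biased, and that arm imbalance materially undermines the planned 90% power. Nor does it follow that a hospital term should be added whatever the allocation. After simple randomisation it costs about 2 power points when hospitals do not differ, and pays only above a share of roughly 5% to 10%.

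**What to change.** In 2.2, replace simple randomisation with 1:1 permuted-block randomisation stratified by hospital, with randomly varying block sizes not disclosed to sites. The same institute can generate the list. In 2.7, add hospital as a fixed effect to the general linear model for the NIH-CPSI and IPSS changes. The two changes belong together.

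Cost: one new list, one model term (4 df), and slightly more predictable allocation because the acupuncturists know the treatment. N stays at 60.

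If patients have already been allocated by simple randomisation, which the recruitment dates in 2.3 make possible, treat the hospital term as optional. Decide on it and record the decision before unblinding.

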**Figure 1 F1:**
[figure not shown]
Flowchart of the trial.

**Figure 2 F2:**
[figure not shown]
Standard Protocol Items: Recommendations for Interventional Trials (SPIRIT).

### Study population and recruitment

2.3

Sixty participants will be recruited from September 2018 to September 2019 through posters, hospital websites, and networks. Recruitment will be conducted by research assistants.

Each participant will have a medical history, physical examination, prostatic fluid cultures, prostate-specific antigen evaluation, urine flow rate, and residual urine examination. Microbiology of the prostatic fluid/urine specimen will be collected by the 2-glass test.^[29]^ A urologist will be responsible for diagnosis.

The criteria for inclusion in this study are the following: aged 18 to 50 years; with CP/CPPS, diagnosed according to the NIH CP/CPPS consensus (discomfort or pain in the pelvic region ≥3 months during the previous 6 months^[4]^); and NIH-CPSI total score ≥15. Potential participants will be excluded for any of the following: urologic disease; residual urine volume ≥100 mL, Qmax ≤15 mL/s; use of 5-alpha reductase inhibitor, alpha-blockers, antibiotics or any other prostatitis-specific medication during the previous 1 month; diseases that influence urologic symptoms; or any acute disease or severe disease requiring treatment. Urologic diseases that will prevent inclusion are bladder outlet obstruction, overactive bladder, neuropathic bladder, interstitial cystitis, cystitis glandularis, bladder cancer, acute prostatitis or bacterial prostatitis, benign prostatic hyperplasia, prostate cancer, symptomatic urinary tract infection, and organic diseases of urinary system. Diseases that influence urologic symptoms are multiple sclerosis, multiple system atrophy, stroke, Alzheimer disease, Parkinson's disease, spinal cord injury, cauda equina injury, and sexually transmitted disease.

### Interventions

2.4

Participants in both the acupuncture and sham groups will be treated for 4 weeks, with 3 sessions per week, making 12 sessions. Treatment will be performed by acupuncturists who have an official license, with strict training related to the standardization and details of performing treatment. Two acupuncturists each will be responsible for the 2 groups. The use of drugs or other therapies for CP/CPPS will be avoided during the study period, unless the symptoms of participants are intolerable. The medications used should be recorded in detail.

#### Acupuncture group

2.4.1

Development of the acupuncture protocol was based on the consensus of acupuncturists from Guang’anmen Hospital. The locations of the acupoints are in accordance with the World Health Organization standard acupuncture point locations.^[30]^ Bilateral Shenshu (BL23), Zhongliao (BL33), Huiyang (BL35), and Sanyinjiao (SP6) will be inserted using Hwato-brand (Suzhou Medical Appliance Factory, China) disposable acupuncture needles (sizes 0.30 × 75 and 0.30 × 40 mm). With patients prone, after routine sterilization, bilateral Zhongliao (BL33) will be inserted to a depth of 50 to 60 mm with a 30° to 45° angle in an inferomedial direction using needles (0.30 mm in diameter, 75 mm in length). Bilateral Huiyang (BL35) will be inserted to a depth of 50 to 60 mm with a slightly superolateral direction using needles (0.30 mm in diameter, 75 mm in length). Bilateral Shenshu (BL23) and Sanyinjiao (SP6) will be inserted vertically to a depth of 25 to 30 mm using needles (0.30 mm in diameter, 40 mm in length). Manipulation of the needles by lifting and thrusting combined with twirling and rotating evenly will be performed until deqi occurs, defined as a sensation of soreness, numbness, heaviness, and ache.^[31]^ Manipulations will be applied every 10 minutes and each session will last for 30 minutes.

#### Sham acupuncture group

2.4.2

Bilateral sham BL 23, BL 33, BL 35 (15 mm to BL23, BL33, and BL35) and SP6 (10 mm to SP6) will be inserted by needles (0.20 mm in diameter, 25 mm in length) to a depth of 2 to 3 mm without manipulation.

### Outcome measurement

2.5

The 3 coprimary outcomes are the change from baseline in total NIH-CPSI score measured respectively by the 3 assessment modes after the 4-week treatment.^[13]^ The NIH-CPSI has a total possible score of 43; higher scores indicate more severe symptoms. The 9 items of this scale are stratified into 3 domains as follows: pain/discomfort (location/type, frequency and severity, 0–21 points); urinary symptoms (10 points); and quality of life (0–12 points). The minimal clinically important difference of the NIH-CPSI is 4 points.^[4]^ The 3 modes of assessment are as follows: Mode 1, the scale is recorded at the hospital within 10 minutes after the twelfth (last) treatment of the 4-week treatment period, in the company of the outcome assessors; Mode 2, the scale is recorded the same day, but not at the hospital; and Mode 3, the scale is recorded at the hospital 1 to 3 days after the last acupuncture session. The outcome assessors will be responsible for calling the participants by telephone to remind them to fill the scale after leaving the hospital, and recording the accurate time for filling the scale.

The 3 key secondary outcomes are the 3 modes of assessment of the changes from baseline of the NIH-CPSI total score in the acupuncture group.

The secondary outcomes of this study are the changes from baseline of subscale scores of the NIH-CPSI, and the International Prostate Symptom Score (IPSS). The IPSS (Hong Kong Chinese version 2) is a valid, reliable, and sensitive measure to assess Chinese males, with 7 questions concerning urinary symptoms and 1 question concerning quality of life.^[32]^ The total possible IPSS score is 35 (asymptomatic to very symptomatic). Symptoms evaluated by the IPSS are categorized as mild (0–7), moderate (8–19), or severe (20–35).

The proportions of participants in each response category of the Global Response Assessment (GRA) will be assessed. The GRA comprises 7 response categories: markedly worsened, moderately worsened, slightly worsened, no change, slightly improved, moderately improved, and markedly improved.

The participants’ expectations regarding acupuncture will be measured at baseline. Participants will answer 2 questions: “In general, do you believe acupuncture is effective for treating the illness?”; and “Do you think acupuncture will be helpful to improve your CP/CPPS symptoms?” Participants will choose “Unclear,” “Yes,” or “No” as the answer.

In addition, during the fourth week of the study period (sessions 11 or 12) participants will be asked to answer the following question within 5 minutes after treatment: “Do you think you have received traditional acupuncture in the past weeks?” The participants will be able to choose one of the following options as the answer: “Unclear,” “Yes,” or “No.”

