## Discussion

3

This proposed study will assess the efficacy of acupuncture after 4 weeks of treatment for patients with CP/CPPS, and 3 modes of evaluation of acupuncture efficacy. To our knowledge, almost none of the other recent studies have reported the details of assessment when using scales as the primary outcomes, and it is not clear in which mode the effect of acupuncture was assessed. The objective of the present study proposed here is to evaluate modes of assessment, to improve the repeatability of acupuncture research, and improve the reliability of results.

The results of our previous pilot study^[14]^ showed that, after 8 weeks of treatment, the symptoms of patients with CP/CPPS were clinically improved. However, there is no exact and definitive means of assessment in practical clinical acupuncture research. For example, among studies the timepoints of assessment have varied between immediately or a few days after acupuncture, and the assessment scales may be recorded within or outside the hospital.

In general, acupuncture ameliorates pain immediately and the effect lasts for a few hours.^[33,34]^ However, assessments conducted immediately or soon after treatment may exaggerate the results. In addition, the influence which patients are accompanied with outcome assessors on objective effect assessment cannot be ignored. Meanwhile, personal and situational factors which may affect treatment response^[34]^ should be considered.

In this study, the efficacy of acupuncture will be evaluated at week 4 using 3 assessments modes. Practically however, it is difficult to restrict the time interval for recording any of these too strictly. Hence, the exact time of assessment will be recorded. The timepoint of mode 3 will be regarded as the longest time interval to assess the effect of week 4.

This study has 3 main limitations. Firstly, 4 weeks of treatment with 12 sessions may not be enough for patients, and assessing the efficacy at week 4 will result in some bias. However, this is a preliminary study meant to provide some indications for future acupuncture research when using scales as primary assessment tools. Secondly, it is difficult to blind the acupuncturists to the treatment group, which may bring some bias. Finally, the sample size is small. In future studies, larger sample sizes will be needed and more timepoints will be included within the assessing modes to monitor dynamic changes associated with acupuncture in CP/CPPS.

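### The stated model for the three key secondary outcomes gives no within-patient contrast between assessment modes, and a non-significant test of means would not show that the modes agree

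*Protocol article*

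**What the plan says.** Section 1.1 of the protocol article gives the trial two aims: to determine the efficacy of acupuncture after 4 weeks, "and evaluate 3 modes of assessment of efficacy". The Discussion says that the objective "is to evaluate modes of assessment, to improve the repeatability of acupuncture research, and improve the reliability of results". It also names the worry behind this: "assessments conducted immediately or soon after treatment may exaggerate the results".

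Section 2.5 defines three modes of recording the NIH-CPSI: at the hospital within 10 minutes of the last session with the assessor present, elsewhere on the same day, and at the hospital 1 to 3 days later. The change from baseline under each mode is a coprimary outcome. The section then adds: "The 3 key secondary outcomes are the 3 modes of assessment of the changes from baseline of the NIH-CPSI total score in the acupuncture group".

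Section 2.7 analyses the primary outcome "by fitting a general linear model, with the baseline value as a covariate, and treatment as a fixed effect", and continues: "The same approach was used for the 3 key secondary outcomes and the change from baseline in the IPSS score". The three primary and three secondary hypotheses are tested in a hierarchy, two-sided at 0.05. The six steps are in a supplementary table that is not shown. The article names no contrast between modes, no agreement measure and no equivalence margin.

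**The concern.** The key secondary outcomes are the only place where the article takes up the second aim apart from the comparison with sham, and the method it states there does not fit. A model whose explanatory terms are baseline and treatment estimates a difference between treatment groups. Inside one group that difference does not exist, and the model has no term for mode. It also makes no use of the three readings coming from the same patient.

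Suppose the intention is a test of whether mean change differs by mode. Two limits then remain. Equal group means do not show that a patient would score the same under two modes. And p>0.05 does not show that the means are equal, particularly in one arm of a trial sized for another comparison. Later trials would want to know whether the mode matters and by how much, and a bare non-significant result tells them neither.

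**Working it through.** **The plan's own figure.** Inputs from section 2.7: difference 4, SD 4.5, two-sided alpha 0.05, power 90%, loss 6%. A two-sample t-test needs 27.6, so 28 per group (power 90.4%), and 56/0.94 = 59.6, so 60 in total. The stated figures reproduce, but they are for acupuncture versus sham. No sample size is given for comparing modes.

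**What the stated model estimates in one arm.** The model is change = intercept + b × baseline + c × treatment. In the acupuncture group treatment is the same for every patient, so c cannot be separated from the intercept. Fitted once per mode, the model leaves three separate baseline-adjusted mean changes. It provides no difference between modes and no standard error for one, because that requires the within-patient correlation.

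**What a paired comparison could show.** Inputs and assumptions:

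- n = 28 in the acupuncture group (section 2.7).
- SD 4.5 (section 2.7), assumed to hold under each mode.
- Correlation r between two modes: not in the article, so varied from 0.5 to 0.9.
- Differences roughly normal, with one baseline per patient. The baseline then cancels: the difference in change between two modes equals the difference between the two readings.

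Formulas:

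- SD of the paired difference: SDd = 4.5 × √(2(1 − r)). For r = 0.8 this is 4.5 × √0.4 = 2.85.
- 95% CI half-width: 2.052 × SDd/√28. For r = 0.8 this is 2.052 × 2.85/5.29 = 1.10.
- Limits of agreement with equal means: ±1.96 × SDd. For r = 0.8 this is ±5.6.
- Share of patients differing by 4 points or more with equal means: 2 × (1 − Φ(4/SDd)). For r = 0.8 this is 16%.
- Power: paired t-test at two-sided 0.05.

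| r | SDd | CI half-width | Limits of agreement | Differ by 4 or more | Power, 1-point shift | Power, 2-point shift |
|---|---|---|---|---|---|---|
| 0.5 | 4.50 | 1.74 | ±8.8 | 37% | 21% | 62% |
| 0.7 | 3.49 | 1.35 | ±6.8 | 25% | 31% | 83% |
| 0.8 | 2.85 | 1.10 | ±5.6 | 16% | 43% | 95% |
| 0.9 | 2.01 | 0.78 | ±3.9 | 5% | 72% | over 99% |

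The limits of agreement and the shares are computed at a true mean difference of zero. In every row a test of means would be non-significant 95% of the time, although individual agreement differs widely between rows.

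**Could equivalence of means be shown?** Simulated chance of success for one pair of modes, n = 28, true mean difference zero. The margins are illustrations: 4 points is the important difference in section 2.5, and 2 points is half of it.

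| r | 95% CI within ±2 | Two one-sided 5% tests, ±2 | Two one-sided 5% tests, ±4 |
|---|---|---|---|
| 0.5 | 26% | 48% | 99.7% |
| 0.7 | 67% | 81% | over 99.9% |
| 0.8 | 90% | 95% | over 99.9% |
| 0.9 | over 99% | over 99.9% | over 99.9% |

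Requiring the whole 95% CI inside ±4 succeeds about 99% of the time at r = 0.5 and more often at higher r.

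**The case against.** The strongest reply is that the article nowhere sets out to show agreement or interchangeability. Its stated worry is that early assessment overstates the effect, which is a shift in the group mean, and mean change by mode is a reasonable quantity for that. The repeatability it mentions is that of acupuncture research, which can be read as consistency between trials once the mode is fixed and reported. It calls itself preliminary, lists the small sample as a limitation, and never says that a null result will be read as equivalence. The testing steps are in a supplement, and an analysis plan may exist. All of this stands.

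A reader might therefore infer too much from the calculations, namely that the aim concerning modes cannot be answered at all. The article does not support that: a significant difference between modes would speak directly to the stated worry, and a confidence interval would bound the shift. Nor can one say that no agreement analysis is planned, since the supplement is not visible.

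Two points survive. Section 2.7 does not merely leave the method to another document. It names one, and that method contains no comparison between modes. And the limits on what a null result can show hold whatever the intention, so they are worth settling before the results are read.

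The reply is also right that the size depends on an assumed correlation. At r = 0.9 the limits of agreement fall just inside 4 points.

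**Conclusion.** The point holds in a limited form. As stated, the analysis of the key secondary outcomes yields no within-patient contrast between modes. Read generously as a test of mean differences, it could find a systematic shift but could not show agreement, and p>0.05 must not be taken as equivalence.

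The size rests on SD 4.5 under each mode and an assumed correlation. Over r = 0.5 to 0.8, a true 1-point shift would be missed 79% to 57% of the time, and limits of agreement of ±8.8 to ±5.6 points could accompany identical means. Over r = 0.5 to 0.9 the CI half-width is 1.7 to 0.8 points, so the planned data are informative about the mean shift if they are analysed as pairs.

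This is an inexpensive improvement that should be made. It leaves the acupuncture-versus-sham comparison untouched.

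**What to change.** Replace the reference to the same approach for the three key secondary outcomes with an explicit comparison:

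- For each pair of modes, estimate the within-patient mean difference in the acupuncture group with its 95% CI, from a paired analysis or a repeated-measures model on the three readings with mode as a factor.
- Report, as descriptive measures, the 95% limits of agreement and the share of patients whose scores differ by 4 points or more.
- State that equivalence will be claimed only if the interval lies within a margin fixed in advance, and never from p>0.05. With 28 patients, a 2-point margin is workable only if the correlation is about 0.8 or higher when a 95% CI is required, or about 0.7 with two one-sided tests at 5%. A 4-point margin is attainable over the whole range examined.
- Check that the steps in the supplementary table refer to these contrasts.

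The cost is a change of wording and a small analysis of readings already planned. There are two drawbacks. A margin has to be justified if equivalence is to be claimed. And the modes differ in place, assessor presence and time, so a difference between them mixes these with up to 3 days of real symptom change, and the report should say so.
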